### Variables and their measures

#### Primary outcomes

The primary outcomes for this RCT include cognition, AD signature cortical thickness, functional connectivity in DMN, aerobic fitness, and clinical AD conversion. Cognition and aerobic fitness will be assessed at baseline and at 3, 6, 12, and 18 months; AD conversion (including reversion to normal cognition) at 6, 12, and 18 months; and AD signature cortical thickness and DMN at baseline and at 6, 12, and 18 months (Table 2).

**Table 2 Tab2:** Data collected from participants over time (S: Screening)

Variables	Measures (data types)	Source of data collection	S	Month				
				0	3	6	12	18
Cognitive outcomes								
Executive function	EXAMINER (continuous)	Computer-based and paper based test		x	x	x	x	x
Episodic verbal memory	RAVLT (continuous)	Pencil-paper-based test	x		x	x	x	x
Episodic visual memory	BVMT-R (continuous)	Pencil-paper-based test		x	x	x	x	x
AD conversion-clinical	Consensus diagnosis using 2011 criteria for probable AD (categorical)	All data collected				x	x	x
MCI reversion	ADNI criteria (categorical)	All data collected				x	x	x
MRI mechanistic outcomes								
Cortical thickness	Structural MRI (continuous)	Device measured	x			x	x	x
Functional connectivity in DMN: resting state	fMRI (continuous)	Device measured	x			x	x	x
Aerobic fitness outcomes								
Aerobic fitness	Symptom-limited peak cycle-ergometer test (continuous)	Performance-based test	x		x	x	x	x
Aerobic fitness	10-m ISWT (continuous)	Performance-based test		x	x	x	x	x
Other variables								
Implementation consistency	Consistency checklist (continuous)	REDCap report	Monthly					
Global cognition	MoCA (continuous)	Pencil-paper-based test	x		x	x	x	x
Daily functioning and mood	ADL-PI, WHODAS (all continuous)	Self-report, paper form	x		x	x	x	x
Depression	GDS (continuous)	Self-report, paper form	x	x	x	x	x	x
Medical changes	Medical diagnoses, falls, medications, and health service use (all categorical)	Self-report, paper form	Monthly					
Demographics	Age, education (both continuous), gender, race (both discrete)	Self-report, paper form	x					
Premorbid intellect	WTAR (continuous)	Pencil-paper-based test	x					
Non-study physical and mental activities	Wearable activity monitor, PASE questionnaire, MLA monthly (continuous)	Wrist device; pencil-paper-based questionnaire	Monthly					
Adherence	Percent (continuous)	Paper form	Monthly					

Tests administered during screening will be used as baseline data to avoid practice effects

*AD* Alzheimer’s disease, *ADL-PI* Activities of Daily Living-Prevention Instrument, *ADNI* Alzheimer’s Disease Neuroimaging Initiative, *BVMT-R* Brief Visuospatial Memory Test-Revised, *ISWT* Incremental Shuttle Walk Test, *MCI* mild cognitive impairment, *MLA* mental leisure activity, *MoCA* Montreal Cognitive Assessment, *MRI* magnetic resonance imaging, *PASE* Physical Activity Scale for the Elderly, *RAVLT* Rey Auditory Verbal Learning Test, *WHODAS* World Health Organization Disability Assessment Schedule, *WTAR* Wechsler Test of Adult Reading

#### Cognition

Cognition includes composite scores for executive function and episodic memory, respectively. Executive function will be measured using the EXAMINER, a computerized test package designed for RCTs. It calculates three subdomain composite scores on working memory, cognitive control, and fluency and an overall composite score for executive function [56]. Test-retest reliabilities are .78 to .93 [57]. EXAMINER has three alternative packages to reduce practice effects. Episodic memory will be assessed using the Rey Auditory Verbal Learning Test (RAVLT) [58] and the Brief Visuospatial Memory Test-Revised (BVMT-R) [59]. These tests are similar in format; however, one utilizes verbal learning while the other utilizes visual learning, allowing a comprehensive assessment of visual and verbal memory. A composite score combining immediately and delayed recalls from the two tests will be developed.

#### AD signature cortical thickness and DMN

##### MRI harmonization

Both sites will use 3 T Siemens Prisma scanners (Erlangen, Germany). Quality-control checks on the phantom, volunteer data, and imaging sequences will be conducted before any data collection. MRI data will be analyzed at the CogT Lab at UR.

##### MRI data acquisition

Structural MRI, fluid-attenuated inversion recovery (FLAIR), and blood oxygen level-dependent (BOLD) functional MRI (fMRI) data will be collected in a 30-min session. Each session will begin with a localizer scan, followed by a magnetization-prepared rapid gradient echo imaging (MPRAGE) scan with 1-mm isotropic resolution to provide high-resolution structural-weighted anatomical images. Three-dimensional FLAIR and susceptibility weighted images (SWIs) will be acquired to ascertain brain pathology (e.g., cerebrovascular disease). Field maps will be acquired to correct for distortions in echo-planar imaging sequences. BOLD functional data during resting state will be collected using a gradient echo-planar imaging sequence. The resting-state scan will be acquired using simultaneous multi-slice imaging. Quality control of each MRI session will be performed.

##### Structural MRI data preprocessing and analysis

We will use the structural MRI measure to develop a composite score of AD signature cortical thicknesses segmented and analyzed with FreeSurfer, composing the following individual regions of interest: precuneus, fusiform, and inferior and middle temporal lobes [49].

##### fMRI data preprocessing and analysis

The data will be analyzed using the SPM software package. fMRI preprocessing will consist of motion correction, slice-timing correction, normalization, and Gaussian spatial smoothing. All the regions of interest in the DMN will be extracted based on our and others’ independent component analysis results [50]. To calculate resting-state fMRI, the correlation between each selected region pair will be Fisher Z-transformed and averaged to derive a summary score for DMN strength.

#### Aerobic fitness

Aerobic fitness will be measured as peak oxygen consumption (VO_2peak_) from the symptom-limited peak cycle-ergometer test and the 10-m Incremental Shuttle Walk Test (ISWT) [60]. The participant will begin cycling at a comfortable speed, then encouraged to increase the intensity as the resistance is increased every 3 min (1 metabolic equivalent, = 3.5 ml oxygen/kg body weight/minute). The participant will continue until fatigued or until the test termination criteria are satisfied per the ACSM. VO_2peak_ and peak hemodynamic responses (e.g., HR, heart rhythm, blood pressure) will be continuously monitored via electrocardiogram and indirect calorimetry. The Borg Rating of Perceived Exertion (RPE) will be assessed during the last minute of each stage and at peak exercise. The ISWT will be used as a field test for the evaluation of aerobic fitness. The distance covered in the ISWT has shown correlations with VO_2peak_ obtained from graded exercise tests (*r* = .67–.95) [60].

#### AD conversion or reversion to normal

AD conversion is defined as meeting clinical criteria for AD. Beginning with the 6 months assessment, a consensus clinical diagnosis of AD will be determined using the 2011 probable AD diagnostic criteria [61]: memory deficit (≥ 1.5 standard deviation (SD) below age- and education-corrected norms), Montreal Cognitive Assessment (MoCA) < 18, decline in activities of daily living, cognitive changes not due to other conditions, and observed pathology (e.g., degree of atrophy). MCI reversion to normal cognition will be assessed and treated similarly as AD conversion. At the 18 months follow-up, a final classification will be determined for each participant (e.g., constant as MCI, conversion to AD, reversion to normal) based on the AD Neuroimaging Initiative criteria [62].

#### Covariates

Covariates include implementation consistency, global cognition, medical conditions, non-study physical and mental leisure activities (MLAs), premorbid intellect, and adherence. Covariates were selected for their known relationship with cognition and will be measured with psychometrically sound instruments, but they are not all inclusive since randomization will minimize imbalances among groups.

Implementation consistency between sites will be measured using four indicators: participant accruals (number of respondents, enrolled and per group); baseline characteristics (overall and in each group); adherence to the assigned activity and reasons for not adhering; and time to reach key milestones (e.g., initial contact to each screening step, enrollment to baseline, baseline to first activity session, and duration for completing assigned activity). Global cognition will be measured using MoCA. Medical conditions will be assessed using the Medical Changes, Health Service, and Falls Assessment Form, and will include diagnoses, falls, medications, and health service use. Depression will be measured by the Geriatric Depression Scale (GDS). Non-study physical and mental activities will be measured by the MLA questionnaire, a wearable activity monitor, and the Physical Activity Scale for the Elderly (PASE) questionnaire. Daily functioning and mood will be measured using the Activities of Daily Living-Prevention Instrument (ADL-PI, self-administered) and the WHO Disability Assessment Schedule (WHODAS). Premorbid intellect will be assessed using the Wechsler Test of Adult Reading (WTAR).

### Study procedure

#### Study preparation and randomization

We will develop a Study Operations Manual to ensure implementation consistency across sites. All staff will be adequately trained to ensure participant safety, blinding, data quality, and protocol adherence. Prior to any recruitment, the statistician will create a randomization schedule in REDCap using a random number generator. Qualified participants will be randomized after completing baseline data collection. The study staff (coordinator/interventionist) will log into the REDCap randomization module and enter a participant’s name/site/age. The randomization module will assign the participant to a group and record the assignment in a database that is only accessible to these staff.

#### Data collection

Enrolled subjects will be scheduled to complete baseline data collection. Subsequent data collection will occur at 3, 6, 9, and 12 months for cognition and other outcomes which are further described under “Variables and their measures” and in Fig. 1. Subjects who undergo MRI at baseline will be re-evaluated for eligibility for MRI at 6 and 12 months (Fig. 1). To ensure the blindness of the data collectors from the intervention assignment, the data collectors will not interact with enrolled subjects except for data collection.

#### Delivery of the assigned activity for each group

Within 2 weeks of completing baseline data collection, participants will start their assigned activity: ACT, cycling only, SOP training only, or attention control. Each activity will consist of a total of three weekly, supervised sessions for 6 months (72 total sessions). One interventionist will supervise two to three participants in the same activity. The sessions will be delivered over up to a 28-week period to account for missing sessions due to the data-collection week at 3 months, vacations, and illnesses.

##### Cycling only

Moderate-vigorous intensity will be prescribed using an undulating (non-linear) progression scheme with intensity ranges from 50 to 75% of HR reserve and/or 11–15 on the RPE scale and exercise durations of 30–50 min per session. HR reserve will be calculated by subtracting resting HR (after 10 min of quiet resting) from the peak HR achieved during the symptom-limited peak cycle-ergometer test. Cycling will be set at 50–60% of HR reserve or RPE 11–12 for 30 min in session 1, and will be alternatively increased by 5% of HR reserve (or 1 point on Borg) or 5-min increments as tolerated up to 65–75% of HR reserve (or RPE 13–15) for 50 min per session over time. Participants will do a 5-min cardiac warm-up and cool-down before and after cycling following ACSM guidelines. In each session, the interventionists will equip the participants with wireless HR monitors, take resting HR and blood pressure, and monitor HR, RPE, talking ability, and signs and symptoms of overexertion every 5 min, and blood pressure every 10–15 min. Participants may leave after their HR and blood pressure return to pre-cycling levels. Each month, participants will wear a device on their wrists for 7 consecutive days to track study-unrelated physical activity. The interventionists will help put the device on at the end of a session and take it off before the activity session on day 7.

##### SOP training only

SOP training will involve the use of the InSight online program (Posit Science). This includes five games (Eye for Detail, Hawk Eye, Visual Sweeps, Double Decision, and Target Tracker) that involve multiple cognitive processes, primarily in attention and processing speed. All games share visual components, and the tasks become increasingly difficult and require faster reaction times as they progress. Participants will respond either by identifying what object they see or where they see it. The training will automatically adjust the difficulty of each task based on performance, ensuring that participants always operate near their optimal capacity. The training programs will automatically record the percentage of completion of each game and the scores. The initial training will take longer to allow participants to adapt to the style of cognitive training. Gradually, individuals will require a shorter practice time to retain the training effect. The interventionists will supervise and help with technical problems as needed. Training will occur in a semi-private room, where each participant will have his own workspace, computer, and headset to avoid distraction.

##### ACT

Participants will participate in cycling first and SOP training second without time lapse in each session. Session durations for ACT will be 80 min (sum of session durations for cycling only and SOP training only).

##### Attention control

Participants will participate in stretches and MLAs that we have previously tested and that are matched to session durations for cycling and SOP training, respectively. Stretching includes seated movements and static stretches that induce no changes in aerobic fitness [63]. MLAs include online word search, Sudoku, and solitaire games that are similar to everyday mental activities without the SOP training’s time, speed, or novel cognitive stimuli elements, which are essential for improving cognition [35, 63]. These activities will control for social interaction, computer, and online experience effects of the ACT and increase participant retention.

##### Treatment fidelity

In a multi-site study, ensuring implementation consistency across sites is of paramount importance to reach valid results. This study was designed to ensure treatment fidelity based on the NIH Behavior Change Consortium recommendations [64] and our experience [65]. We will randomly check activity sessions in person using the Fidelity Checklist and retrain staff as needed.

##### Safety, retention, adherence, and validation

We have built in many strategies tested in our preliminary studies to protect participants against risks, including appropriate equipment and personnel training, careful screening and informed consent, frequent communications, individualized prescriptions for cycling and SOP training, supervised and guided sessions, and ongoing monitoring of medical changes. Interventionists will be fully trained using the operations manual and will be able to consult with the investigators immediately as well as at weekly meetings. Our previous work with AD and aMCI achieved 74.3–86.4% adherence to cycling [65] and 100% adherence to SOP [35]. The safety strategies will also ensure retention. For this RCT, we predicted a higher attrition rate (25% at 6 months and 35% at 18 months) than those of our current RCTs with AD and aMCI (4.3–11.1% attrition) [35, 65].

### Data management

#### Data entry, coding, and storage

The principal investigators (PIs) will be responsible for the integrity and validity of the study data. The PIs and the study coordinators will oversee all participant records, adherence to the protocol by all staff, screening, and recruitment logs, percent of exercise sessions attended, missed sessions, compliance, retention, adverse events, and study outcomes. They will also ensure data creation, completeness, quality checks, and audits. The PIs and statistician will develop a data audit to ensure data accuracy and completeness. Participant data will be collected with the verbal or written consent of the participant. Information pertaining to individual participants will be released with the participant’s permission only. All participant data will be identified by a uniquely coded screening ID assigned to each respondent and a study ID for participants eligible for enrollment. Access to the master links between name and screening ID as well as between screening ID and study ID will be restricted to the study coordinator, interventionist, and staff involved in screening.

Data collection forms returned to the research office by the research assistants (RAs) will be reviewed by the study coordinators for accuracy and completeness before entry into REDCap, a MySQL database accessed via a secure web interface. The MySQL database and the web server will both be housed on secure servers operated by the UMN Acadmic Health Center-Information Systems (AHC-IS) or UR Information Technology Services (ITS). The servers are in a physically secure location on campus and are backed up nightly, with the backups stored in accordance with the retention schedule of daily, weekly, and monthly tapes retained for 1, 3, and 6 months, respectively at each university’s information services. Weekly backup tapes are stored offsite. The AHC-IS or ITS servers provide a stable, secure, well-maintained, and high-capacity data storage environment that meets the requirements for storing HIPAA-sensitive data, and both REDCap and MySQL are widely used, powerful, reliable, well-supported systems. Access to the system by username and password will require specific permission from the respective PI or her designee. The PIs and study coordinators will continually work with the study sites to ensure compliance and quality. The PIs will verify data accuracy and completeness in REDCap for data collected at each site. Any missing data will be assigned to a data collector for collection. If a participant withdraws from the study, all attempts will be made to collect data to allow for inclusion in the analysis. Reasons for withdrawal will be recorded.

Data audits of electronic outcome data will be conducted by the PIs and study coordinators. If the PI identifies any discrepancies in scoring between the RA who collected data and the RA who entered data, the RAs must consult the neuropsychologist co-investigator for correct scoring, and the correct scores will be documented on paper and entered into REDCap.

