## Discussion

The RCT is the gold standard design for determining the causal effect of an intervention on an outcome. Alternative designs include cross-over and usual care or waitlist as controls. Cross-over designs are ideal for interventions without carry-over effects, which is not the case for ACT. Usual-care or waitlist controls preclude assessing the placebo or Hawthorne effect of ACT.

A potential problem is unblinding. We have built in four strategies to ensure blinding: randomization using permuted blocks; all investigators blinded to group assignments; all participants blinded to the study aims and reminded as needed not to discuss their experiences with the outcome assessor; and outcome assessors blinded to the study aims, group assignments, and previous test results, and interacting with participants only for data collection [52]. Assessors will not interact with other staff who are not blinded (e.g., exercise interventionists) and will participate in separate meetings. Blinding success will be assessed after each data collection: Was group assignment unveiled? Why? For participants whose group assignments are revealed, a different blinded assessor will collect subsequent data. Other strategies include the use of standardized protocol, operations manual, forms, and reliable and valid variable measures. The analyses will incorporate all design features (e.g., site, repeated measures within persons, missing data).

While our aims are not focused on age and sex, we will take two measures to ensure adequate attention to them. First, we will stratify enrollment by age and target an enrollment of 60% women, because age and gender are established risk factors for AD [66]. Second, we will conduct an exploratory analysis examining whether age and sex moderate intervention effects on outcomes. We do not intend a fully powered analysis of this question for this RCT. However, large age/sex differences may be discernible and generate hypotheses for subsequent studies.

We do not plan to emphasize single-domain vs. multiple-domain MCI phenotype when identifying our sample given the change of emphasis in the updated NIA-Alzheimer’s Association (AA) criteria [3, 67]. However, we will secondarily examine the effect of the intervention on these phenotypes to specify a subsample who may benefit, particularly if the proposed intervention is effective for improving primary cognitive outcomes.

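### The assessor blind does not extend to the coordinators' accuracy review and audit of outcome forms

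*Protocol article*

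**What the plan says.** On allocation, Study preparation and randomization states that "the statistician will create a randomization schedule in REDCap using a random number generator". The allocation itself is performed by others: "The study staff (coordinator/interventionist) will log into the REDCap randomization module". The module is then to "record the assignment in a database that is only accessible to these staff".

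On identification, Data entry, coding, and storage says that access to the links from name to screening ID and from screening ID to study ID is "restricted to the study coordinator, interventionist, and staff involved in screening".

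On outcome forms, the same section says that forms coming back from the research assistants "will be reviewed by the study coordinators for accuracy and completeness before entry into REDCap". It adds: "Data audits of electronic outcome data will be conducted by the PIs and study coordinators". If the principal investigator finds that the collecting and the entering research assistant scored differently, "the RAs must consult the neuropsychologist co-investigator for correct scoring".

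On blinding, the Discussion lists investigators and outcome assessors as blinded to group, and participants as blinded to the study aims. It also states: "Assessors will not interact with other staff who are not blinded (e.g., exercise interventionists) and will participate in separate meetings". Coordinators do not appear among the blinded.

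**The concern.** Participants know which activity they attend, so protection against detection bias rests largely on outcomes being measured and recorded by people who do not know the arm. A check for accuracy differs from a check for completeness: it asks whether the score is right, and so invites a view on the score. If the checker can know the arm, scores that look surprising for that arm may get closer attention than others.

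The outcomes exposed are those scored by hand. Table 2 lists the RAVLT, the BVMT-R and the MoCA as pencil-and-paper tests and the EXAMINER as partly paper. The episodic memory composite is built wholly from the RAVLT and BVMT-R, and it is one of the two Aim I outcomes. Memory deficit and MoCA cut-offs also enter the criteria for AD conversion.

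**Working it through.** There is no arithmetic to reproduce. The check is to set the role descriptions side by side.

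1. **Who can know the arm.** The statistician generates the schedule, but the coordinator/interventionist executes each allocation, and the assignment database is open to that group of staff. A coordinator who has performed an allocation cannot be blind to it.

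2. **Whether coded forms hide the participant.** For the coordinator they do not. The ID links are open to that role, so a form carrying a study ID can be traced to a participant and then to an arm.

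3. **What the coordinator does with outcome data.** There are two tasks: review of returned forms for accuracy as well as completeness, before entry, and a share in auditing the electronic outcome data. The same section also gives coordinators, with the principal investigators, oversight of session attendance and of study outcomes.

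4. **Whether the blinding strategies reach this step.** The Discussion names four: permuted blocks, blinded investigators, participants blinded to the aims, and blinded assessors who meet participants only to collect data. All of these act up to the point of collection or concern other roles. None covers the coordinator's review. Research assistants handing forms to an unblinded coordinator also fits poorly with the separation of assessors from unblinded staff, although no direct exchange between them is described.

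5. **Whether a later safeguard catches it.** The one stated route for settling scores compares the collecting with the entering research assistant. The coordinator's review comes before entry. If a doubt raised there led to an amended form, the entering research assistant would work from the amended form and no discrepancy need appear. The article does not say what happens when the coordinator's own review raises a doubt.

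6. **Whether the effect would cancel.** Randomization follows baseline data collection, so no arm exists when the baseline tests are done, but there is one at 3 and 6 months. Arm-aware review would therefore bear mainly on follow-up scores. Aim I analyses change from baseline to 3 and 6 months, so a difference by arm would enter the change directly.

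**The case against.** The strongest reply is that the blind is intact where it matters most. Data collectors meet participants only to collect data, do not know the arm or previous results, and are replaced if the assignment is revealed. The only described correction of a score starts with a principal investigator and ends with the neuropsychologist co-investigator, both covered by the stated blinding of all investigators. Part of the EXAMINER is computerised. AD conversion is a consensus diagnosis serving an exploratory aim. All of this stands, and it limits the point to one handling step.

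A reader might infer more: that the cognitive scores as a whole lack the protection of blinding, that coordinators decide which scores are queried or corrected, that they send missing items back to collectors, or that every coordinator sees every assignment. The text does not support these. Administration and first scoring are blinded. No passage gives coordinators power over a score. The sentence on missing data names no one as assigning it, and follows one about the principal investigators. The expression coordinator/interventionist, in a two-site trial, does not establish access for each coordinator.

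It can also be said that comparing two research assistants' scores might reveal an altered value. It might, if the comparison used the collector's untouched score, but the article does not say so.

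Finally, locking of forms and user rights are normally left to an operations manual, and their absence from an article is no fault. The point does not rest on such silence. The article itself assigns the accuracy review and the audit to a role with access to assignments.

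**Conclusion.** The point holds in limited form. By the article's own allocation of roles, staff who can know the arm review outcome forms for accuracy before entry and share the audit of outcome data, and the stated blind does not cover that step. This is an avoidable route to detection bias in hand-scored follow-up tests. It is not evidence that bias will occur, and it does not undo the blinding of the assessments themselves.

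Its size cannot be stated: the documents give nothing on scoring error or on how often forms are queried. The conclusion assumes that at least some coordinators who review forms also have assignment access, which is the natural reading of the randomization section, and that hand scoring leaves some room for judgement, which the provision for resolving scoring differences implies. It is worth correcting but is not a fatal flaw.

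**What to change.** Reword Data entry, coding, and storage as follows:

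- Coordinators with access to assignments check outcome forms for completeness only. Their oversight of study outcomes and their part in quality checks and audits are limited in the same way.
- Accuracy review, scoring queries and the audit of outcome scores go to people without assignment access who are already in the workflow: the entering research assistant, the principal investigators and the neuropsychologist co-investigator.
- The text states that the entering research assistant is blinded, which it does not say now.
- Any change to a score after first scoring is logged.

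The change relies on the stated blinding of all investigators. Because the same section has the principal investigators oversee session attendance, those records should reach them in a form that does not show the arm.

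The cost is wording, user rights in REDCap and some checking time moved from coordinators to research assistants. No new role is needed.
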